Within the third stage, the participant will first complete a pre-survey. They will then be instructed to read some materials to learn about analytical writing, and then practice what they have learned by writing an analytical essay as their homework assignment. During practice, the instructions will outline the writing prompt, writing requirement, time requirement, grading feedback, and grading rubric. Specifically, the participant will be asked to write a 350–600-word essay stating whether they agree or disagree with the writing prompt. The time requirement will explain that there is no time limit, but participants are recommended to spend 30 min on the task. We intentionally designed the writing task without a time limit to better reflect a typical homework setting, in contrast to an exam setting where time is constrained. This distinction may elicit different writing behaviors and patterns of using AI tools. For grading feedback, the instructions will explain that the participant will receive their writing score, the class average, and writing feedback from expert instructors once the entire experiment ends. Participants in the intervention group can use ChatGPT to support their writing. Specifically, we choose GPT-4 because it has been independently benchmarked for its standalone performance on analytical writing in the Graduate Record Examinations (GRE), as documented in OpenAI’s technical report [31]. This provides a reference point for us to evaluate the analytical writing capabilities during human-generative AI collaboration. Participants in the control group will complete the writing task without AI assistance. After the writing task, the participant will complete a post-survey. The entire study will last for approximately 1.5 h for each participant.

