## Data collection and management

### Plans for assessment and collection of outcomes {18a}

Data will be collected from multiple sources: pre- and post-survey responses as well as the final essay via the Qualtrics platform, interaction logs with ChatGPT for the intervention group, writing data in the text editor for the control group, gaze and pupil-related data from the eye tracker, and hemodynamic activity data from the fNIRS. In particular, the surveys will capture participants’ background characteristics that may contribute to heterogeneity effects (Table 2). The pre-survey will include measures such as participants’ initial interest in analytical writing and their motivation to achieve a high score on the writing task. The post-survey will include participants’ frequency of ChatGPT use, English ability, their native language, writing ability, critical thinking ability, and demographic details, including their age, gender, race, academic year, and academic major. Background characteristics are mainly collected in the post-survey, unless necessary to be in the pre-survey, to avoid potential signaling effects that could influence participants’ writing behavior during the writing task. The data retrieved from all sources will be anonymous. Data downloaded will be stored on an encrypted and secure server. The data will be deleted 5 years after the study has been completed.

**Table 2 Tab2:** Background information in the pre- and post-surveys

Survey	Construct	Items and response
Pre-survey	Initial interest in analytical writing	On a scale of 1 to 7, how much do you agree or disagree with the following statements? (1 being “strongly disagree” and 7 being “strongly agree”) 1. I find analytical writing enjoyable 2. I enjoy writing an analytical essay 3. I like learning new skills about analytical writing
	Motivation to achieve a high score in the writing task	On a scale of 1 to 5, how motivated are you to achieve a high score in your essay? (1 being “not at all motivated” and 5 being “extremely motivated”)

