For the secondary outcomes, all survey scale measures will be treated similarly to the writing performance outcome. They will be viewed as continuous variables and analyzed using OLS regression with heteroskedasticity-robust standard errors. Cognitive effort, as measured by changes in the cortical hemodynamics, will be treated similarly to pupil size changes. Through a series of pre-processing steps, we will compute channel-wise hemodynamic changes in HbO using the Satori software. The raw data of two wavelengths (760 nm and 850 nm) will be trimmed so that only the fNIRS data collected during the writing task is analyzed, and bad channels will be rejected using a coefficient of variation (CV) [54]. Then, the data will be further pre-processed using a standard pipeline, including data conversion using modified Beer-Lambert law (MBLL) [55], spike removal using a robust spike detection method, motion correction using the Temporal Derivative Distribution Repair (TDDR) [56], physiological noise removal using the highest correlated channel data from the eight short channel data, temporal filtering, and normalization through the z-normalization step. After pre-processing, we will use a generalized linear mixed model to estimate the intervention effect to account for participant-level random effects.

For the above statistical modeling, we will first run the analyses without adjusting for covariates because randomization, on average, eliminates confounding. Subsequently, we will run the analyses with adjusted covariates, including participants’ self-reported skill levels and motivation, because power can often be improved with covariate adjustments, and such adjustments can improve residual confounding. For skill levels, we will include three variables based on the three aspects of self-reported skill level: writing ability, critical thinking ability, and English language ability. For motivation, we will include one variable based on participants’ self-reported motivation to achieve a high-performance score in the analytical writing task. The four variables will be viewed as continuous variables and all added to the model. Should there be variations in other baseline measures, such as gender and race, between the intervention group and the control group, we will further adjust our model to control for these potential confounding sources.

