### Methods for additional analyses (e.g., subgroup analyses) {20b}

We will estimate complier average causal effects (CACE) on the primary outcomes. We will also conduct subgroup analyses to examine heterogeneous intervention effects, provided that sufficient sample sizes can be recruited in each group. The variables of interest are prior skill levels in writing ability, critical thinking ability, and English language ability, as well as motivation. Each of these variables will be examined independently. Additionally, we will take advantage of the pupil size data collected throughout the writing task to explore the intervention effect on cognitive effort across various self-allocated sub-tasks, such as writing the essay, reading the essay, and prompting ChatGPT.

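### Three of the four adjustment covariates, which also define the 'prior' skill subgroups, are self-reported after the writing task, so the adjusted and skill-subgroup estimates are open to post-treatment bias of unknown size and direction

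*Protocol article*

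**What the plan says.** **Covariates.** Section {20a} runs each analysis unadjusted first and then adjusted. For skill, "we will include three variables based on the three aspects of self-reported skill level: writing ability, critical thinking ability, and English language ability". The fourth covariate is a single self-rating of how strongly the participant wants to score well. All four enter as continuous terms. The section then speaks of gender and race as further baseline measures, so it treats the four as baseline too.

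**Subgroups.** Section {20b}: "The variables of interest are prior skill levels in writing ability, critical thinking ability, and English language ability, as well as motivation".

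**Timing.** Section {18a} separates the four. Before the task: "The pre-survey will include measures such as participants’ initial interest in analytical writing and their motivation to achieve a high score on the writing task". After it: "The post-survey will include participants’ frequency of ChatGPT use, English ability, their native language, writing ability, critical thinking ability, and demographic details". Table 2 confirms this placement. The description of the session under Trial design {8} gives the order: "After the writing task, the participant will complete a post-survey".

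**Reason for the timing.** Section {18a}: "Background characteristics are mainly collected in the post-survey, unless necessary to be in the pre-survey", the aim being "to avoid potential signaling effects that could influence participants’ writing behavior during the writing task".

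No section says what the late collection means for adjustment or subgrouping.

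**The concern.** Covariate adjustment in a randomised trial is safe when the covariate cannot have been affected by the allocated condition. Section {20a} justifies adjustment by power and by residual confounding, and both arguments need that condition. Here three of four covariates are recorded after exposure.

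The exposure is most evident for English ability, where the participant judges how well they can produce text just after producing one with or without ChatGPT. The same post-survey asks, as a secondary outcome, for writing self-efficacy, including grammar, spelling and putting ideas into words. The trial therefore tests whether the condition changes one set of self-judgements about writing while treating a neighbouring one as fixed.

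If the rating moves, participants with the same recorded skill are no longer comparable across arms. Adjusted and unadjusted results could then differ for reasons other than precision, and section {20a} does not say which prevails. Effect modification by skill, which is part of a stated objective ({7}), would be read from groups partly formed by the treatment.

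**Working it through.** **Step 1: count and timing.**

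| Covariate in {20a} | What Table 2 asks | When |
|---|---|---|
| Motivation | Rating, 1 to 5 | Pre-survey |
| English ability | Self-rated proficiency, four levels | Post-survey |
| Writing ability | Essay-writing frequency over the past month, four levels | Post-survey |
| Critical thinking ability | Training history, four levels | Post-survey |

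Three of four are post-task. One of those three is a rating of current ability; two are reports of history.

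**Step 2: the plan's own figure, to fix the scale.** Section {14} uses d = 0.45, SD 1, alpha 0.05 (two-sided assumed) and power above 0.8. Per arm, n = 2(1.960 + 0.842)²/0.45² = 77.5, so 78, or 156 in total. With the t distribution it is 79 per arm, 158 in total. At 80 per arm, power is 0.81. The stated 160 reproduces and is not in dispute.

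**Step 3: bias.** Let τ be the true effect, δ the shift in the covariate caused by the intervention (in covariate SDs), and γ the within-arm slope of the outcome on the covariate. The adjusted coefficient then tends to τ − γδ. In the same linear model the contrast at a fixed value of the covariate is also τ − γδ, so stratifying carries the same bias, approximately so with coarse categories. The documents give neither δ nor γ; every value below is an assumption. One covariate, τ = 0.45:

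| δ | γ = 0.2 | γ = 0.3 | γ = 0.5 |
|---|---|---|---|
| −0.2 | 0.49 | 0.51 | 0.55 |
| 0 | 0.45 | 0.45 | 0.45 |
| 0.1 | 0.43 | 0.42 | 0.40 |
| 0.2 | 0.41 | 0.39 | 0.35 |
| 0.3 | 0.39 | 0.36 | 0.30 |

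**Step 4: several covariates.** Biases from single-covariate models cannot simply be added, because the slopes in the joint model are partial. Take three skill items with mutual correlation 0.3, each correlated 0.3 with the outcome (motivation left out). Each partial slope is 0.3/(1 + 2 × 0.3) = 0.1875.
- Only English shifts, by 0.2: 0.45 − 0.1875 × 0.2 = 0.41.
- All three shift by 0.2: 0.45 − 3 × 0.1875 × 0.2 = 0.34.

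**Step 5: simulation.** N = 160, one covariate, γ = 0.3, OLS with robust standard errors, alpha 0.025 as in {20a}, 4,000 replicates:

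| True effect | δ | Mean estimate | Rejection rate |
|---|---|---|---|
| 0.45 | 0 | 0.450 | 0.76 |
| 0.45 | 0.2 | 0.390 | 0.63 |
| 0 | 0 | 0.001 | 0.024 |
| 0 | 0.2 | −0.060 | 0.038 |

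If the self-report instead follows the participant's own performance, at 0.2 to 0.5 units per outcome SD, a true 0.45 is estimated as 0.41 to 0.34. Under a true null that mechanism does no harm (rejection rate 0.022 at 0.5).

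**The case against.** **Two items are history.** One essay cannot change how often someone wrote last month or what training they have had; only the reporting could drift. A reader might infer that all three covariates are ability ratings that ChatGPT would move. Table 2 does not support that. This stands and narrows the point mainly to English ability, whose top level, native speaker, is itself hard to move.

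**The size is assumed.** If a four-level item has an SD of 0.7 to 1.0 (an assumption), a shift of 0.1 to 0.3 SD means a net 7% (0.1 × 0.7) to 30% (0.3 × 1.0) of the ChatGPT arm answering one level higher. That is hard to believe for training history. The shift could be zero, or negative if participants who leaned on ChatGPT rate themselves lower. This stands: the tables in the working show a mechanism and do not forecast this trial's bias.

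**An unaffected analysis comes first.** The unadjusted intention-to-treat estimate is run before any adjustment, subgroup work is conditional on adequate numbers, and {8} calls the framework exploratory. This also stands. A reader might infer that the main comparison has lost the protection of randomisation; it has not.

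**The timing was deliberate.** The stated worry is influence on writing behaviour, which goes beyond any mention of ChatGPT, so asking about writing and critical thinking immediately before a graded essay could prime participants. Collecting the items at sign-up would cut across the separation of experimental from scheduling data in {19} and {27}. This limits the available remedies. It does not make the late items safe to treat as baseline.

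**Conclusion.** The point holds in a limited form. The protocol fixes the timing, the covariates and the label, and these do not fit together: three of four covariates are post-task self-reports used as if they were baseline. The adjusted and skill-subgroup estimates are exposed to a bias of about −γδ. The exposure is plausible for English proficiency and smaller for the two history items.

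The documents determine neither size nor direction. With no shift there is no bias. With an assumed shift of 0.2 SD and slope of 0.3, a true 0.45 becomes 0.39, a loss of 0.06/0.45 = 13%; a shift of −0.2 gives 0.51. These figures assume a linear model and the planning effect for writing performance; the protocol found no prior effect size for the physiological measure of cognitive effort.

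The unadjusted intention-to-treat result does not depend on any of this. The matter should be corrected, but it does not threaten the main comparison.

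**What to change.** In {20a}:
- State that the unadjusted model takes precedence if the two disagree.
- Restrict the main adjusted model to variables measured before the task, namely motivation and initial interest.
- Compare the three skill items between arms and report the comparison.
- Report the skill-adjusted model as a sensitivity analysis, without calling the items baseline.

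In {20b}, drop the word prior for the three skill items and report those subgroups as exploratory, read alongside the arm comparison.

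Where still feasible, collect the three items before the task in a way that respects both the signalling concern in {18a} and the data separation in {19} and {27}. That step needs design thought; the analysis changes above do not depend on it.

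**Cost.** The analysis changes are wording only. The downside is some precision if the skill items are prognostic and in fact unaffected by treatment. At alpha 0.025 and 80 per arm, power is about 0.72 unadjusted and about 0.76 with one unaffected covariate of assumed slope 0.3. Adjustment for motivation and initial interest may recover part of that.

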### Trial design {8}

Our study is a parallel RCT that compares the effects of using ChatGPT (intervention group) versus not using ChatGPT (control group) in an analytical writing task (Fig. 1). Participants will be randomized in a 1:1 ratio. The study follows an exploratory framework.

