### Sample size {14}

To estimate the required sample size, we conducted a simulation analysis on the intervention effect on writing performance using ordinary least squares (OLS) regression. Recent empirical evidence suggests that the effect size of generative AI on writing tasks ranges around Cohen’s *d* = 0.4–0.5, such as [1, 48]. In our simulation analysis, the simulated data assumes normally distributed data, equal and standardized standard deviations between the two conditions, and an anticipated effect size of Cohen’s *d* = 0.45. In the end, our analysis indicated that recruiting a minimum of 160 participants would be necessary to achieve a statistical power greater than 0.8 under an alpha level of 0.05. The simulation was implemented in R, and the corresponding code is available at the Open Science Framework (OSF) via https://osf.io/9jgme/.

We opt to base our sample size estimation on writing performance, but not on the other primary outcome, cognitive effort, for two reasons. First, the effect of generative AI on performance outcomes has been studied [1, 48], but we did not find prior evidence on the effect size of generative AI on cognitive effort using physiological measures. Second, our physiological measure of cognitive effort may likely be powered once the sample size satisfies our behavioral measure of writing performance. Pupillometry studies on cognitive efforts, such as the N-back test, typically recruit 20–50 participants in short, repeated, within-subject trials (e.g., [49]). These studies provide a general estimation of participants needed. Although our study design (i.e., a between-subject RCT) differs from common pupillometry studies, cognitive effort is still a repeated outcome measure using time series pupil data throughout the entire writing process. Repeated outcome measures generally can enhance statistical power by taking into account within-subject variability [50].

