## Statistical methods

### Statistical methods for primary and secondary outcomes {20a}

Here, the intervention effect on the two primary outcomes will be estimated by an intent-to-treat analysis. Our first primary outcome, writing performance, will be treated as a continuous variable. Our second primary outcome, cognitive effort as measured by mean changes in pupil size, will also be treated as a continuous variable. We will estimate the intervention effect on each outcome separately using ordinary least squares (OLS) regression with heteroskedasticity-robust standard errors. To control for type I error inflation due to multiple testing, we will apply a Bonferroni correction. Accordingly, the adjusted significance threshold is set at *α* = 0.05/2 = 0.025. The outcome of cognitive effort is a psychophysiological measure recorded throughout the entire writing process. Standard pre-processing steps will be taken before the statistical analysis [51, 52], such as correcting for screen angle distortion, removing invalid data that do not reflect the actual pupil size (pupil size below 1.5 mm or over 9 mm [53], often due to blinking), smoothing to remove small oscillatory and noise activity, interpolating blink related invalid data, downsampling, and correcting pupil size changes based on the baseline pupil size that will be collected during a 30-s relaxation task at the beginning of the experiment. Participant-level data will be excluded if the data do not meet basic quality standards, such as having a high proportion of invalid data.

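### Each primary outcome gets up to three models and none is named as the 0.025 test; the imbalance-triggered covariate step should give way to a fixed list

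*Protocol article*

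**What the plan says.** All of this is in the protocol article, section {20a}, unless noted.

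- **Threshold.** Each primary outcome (writing score, mean pupil-size change) is analysed by OLS with robust standard errors. The plan says "To control for type I error inflation due to multiple testing, we will apply a Bonferroni correction", and it divides 0.05 by the two outcomes to get 0.025.
- **Model 1, unadjusted.** "we will first run the analyses without adjusting for covariates because randomization, on average, eliminates confounding".
- **Model 2, four covariates.** Self-reported writing, critical thinking and English ability, plus motivation, all enter as continuous variables. The reasons given are power and residual confounding.
- **Model 3, triggered.** "Should there be variations in other baseline measures, such as gender and race, between the intervention group and the control group", those measures are added as well. No cut-off defines a variation, and the list is open.
- **Timing of covariates.** Section {18a} and Table 2 put motivation and initial interest in the pre-survey. The three ability items, gender, race and native language are in the post-survey.

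**The concern.** A threshold controls error only for a test that is fixed before the results are seen. The Bonferroni division covers two outcomes. It does not cover a choice among up to three p-values for the same outcome, and no sentence removes that choice. The text gives some support to either of the first two models: the unadjusted one comes first and is justified by randomization, while the adjusted one is recommended for power.

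The trigger adds a second source of discretion. Exact balance is almost never seen, so whether model 3 exists depends on a cut-off that someone sets later. It also picks covariates by the wrong criterion. Adjustment gains precision when a covariate predicts the outcome; a chance difference between arms says nothing about that.

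At stake is whether a positive claim on a primary outcome has the error rate that the plan promises.

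**Working it through.** **Step 1: the plan's own figures.** Inputs from Sample size {14}: "an anticipated effect size of Cohen’s *d* = 0.45", "equal and standardized standard deviations between the two conditions" (so SD = 1), and a sample "to achieve a statistical power greater than 0.8 under an alpha level of 0.05". Trial design {8} gives 1:1 allocation. Two-sided testing is assumed.

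- n per arm = 2(1.96 + 0.84)² / 0.45² ≈ 78, or 156 in total. The exact t-test gives 79 per arm, or 158. The stated 160 is reproduced, with t-test power 0.808 at 80 per arm.
- Threshold: 0.05/2 = 0.025. For two independent outcomes with one test each, 1 − (1 − 0.025)² = 0.0494.

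The sample-size simulation describes two conditions and no covariates, so it matches the unadjusted model.

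**Step 2: error rate of each model and of a free choice.** The document gives no covariate R2, number of candidate measures or imbalance cut-off, so these are assumptions: R2 of the four named covariates 0 to 0.4 (R2a); R2 of six other measures 0 to 0.3 (R2b); a measure is added when its between-arm p-value is below 0.05, 0.10 or 0.20. Null trials with 80 per arm, independent normal covariates, OLS with HC3 errors, 12,000 runs per row, rejection at p < 0.025:

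| R2a | R2b | cut-off | unadjusted | four covariates | triggered | either of first two | any of three |
|---|---|---|---|---|---|---|---|
| 0 | 0 | 0.05 | 0.024 | 0.022 | 0.022 | 0.026 | 0.027 |
| 0.1 | 0.05 | 0.05 | 0.027 | 0.026 | 0.026 | 0.036 | 0.037 |
| 0.2 | 0.1 | 0.05 | 0.024 | 0.024 | 0.021 | 0.036 | 0.037 |
| 0.3 | 0.1 | 0.05 | 0.024 | 0.023 | 0.021 | 0.038 | 0.039 |
| 0.2 | 0.3 | 0.05 | 0.025 | 0.024 | 0.018 | 0.035 | 0.037 |
| 0.2 | 0.3 | 0.20 | 0.021 | 0.020 | 0.010 | 0.031 | 0.035 |
| 0.4 | 0.2 | 0.10 | 0.026 | 0.020 | 0.014 | 0.038 | 0.040 |

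The Monte Carlo standard error of an entry near 0.0375 is √(0.0375 × 0.9625 / 12,000) ≈ 0.002. With HC1 errors, which the plan's wording also permits, the last column is about 0.035 to 0.041 for prognostic covariates.

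**Step 3: two independent outcomes.** Use 1 − (1 − p)².

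- Any of three, prognostic covariates: p = 0.035 gives 0.069 and p = 0.041 gives 0.080, against 0.05.
- Any of three, no covariate prognostic: p = 0.0274 gives 0.054.
- Unadjusted or four-covariate only: p = 0.0314 gives 0.062 and p = 0.0375 gives 0.074. Most of the excess is already present without the trigger.

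**Step 4: standard errors of the triggered model.** Mean standard error divided by the true SD of the estimate:

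- R2b = 0 and 0.05: 0.1639/0.1614 = 1.015 and 0.1556/0.1534 = 1.014. HC3 alone gives about as much in the four-covariate model (0.1629/0.1607 = 1.014).
- R2b = 0.1: 1.03 to 1.05.
- R2b = 0.2 to 0.3 with cut-offs of 0.05 to 0.10: 1.06 to 1.07.
- R2b = 0.3 with cut-off 0.20: 0.1424/0.1262 = 1.13.

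Coverage of its 95% intervals was 95.2% to 97.4%. The errors were never too narrow on average.

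**Step 5: how often the trigger would fire.** As an example cut-off, take a standardized difference of 0.2. Its standard error is √(2/80) = 0.158, so one measure exceeds 0.2 with probability 0.206, and at least one of six independent measures does so with probability 1 − 0.794⁶ ≈ 0.75. At p < 0.05 the trigger fires in about 27% of simulated trials. How often model 3 appears is therefore set by the missing cut-off.

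**The case against.** The strongest reply is that the unadjusted model is the test by implication. The threshold is set before any covariate is mentioned, the unadjusted model is run first with a reason, and the sample size rests on a comparison without covariates. On that reading the other two models are sensitivity analyses and 0.025 holds. This lean is real, but it is not stated, and the same paragraph argues for adjustment.

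Second, Trial design {8} calls the study exploratory, and section {17a} masks assignment from the analyst. Both soften the point. Neither removes it: the plan sets a formal error threshold all the same, and a two-sided p-value is the same whichever arm label is hidden, so masking does not hide which model crosses 0.025.

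Third, a statistical analysis plan often names the primary model. That is fair for a missing detail. Here the protocol itself states both a threshold and a data-dependent modelling rule, and section {31c} describes the document as the full protocol.

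Three stronger readings are tempting and not supported:

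- *The 0.025 threshold fails outright.* It fails only if the claim may rest on any of the models. No sentence says that it may, and each model alone is at about 0.025 or less.
- *The triggered model gives false positives.* The trigger looks at covariates and arm, not at the outcome. Its errors are too wide if they are wrong at all, and the effect is negligible unless the added measures are clearly prognostic.
- *An imbalance will always be found.* That is true only if any nonzero difference counts; with a cut-off, many trials would not trigger.

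Nor does Bonferroni need to divide by the number of models, provided one is named and the rest are labelled as sensitivity analyses.

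**Conclusion.** The point stands in limited form. The plan promises 0.025 per primary outcome and leaves open which of up to three models is tested at that level, with an undefined data-dependent rule for the third. If any may count, per-outcome error is about 0.035 to 0.041, and about 0.07 to 0.08 over two independent outcomes. If no covariate is prognostic, the figures are about 0.027 and 0.054. All of these rest on assumed R2 values, six candidate measures, assumed cut-offs and independent outcomes; the document gives none of them.

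The larger part of the excess comes from choosing between the unadjusted and four-covariate models, so naming the test matters more than removing the trigger. The case against the trigger is that it is undefined and selects by chance imbalance. It is a conservative and inefficient step, not an error-inflating one. The plan should be changed, but the design is not threatened.

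**What to change.** 1. Name one prespecified model per primary outcome as the test at 0.025, and label every other model a sensitivity analysis. Either an unadjusted or a fixed adjusted model protects the threshold; with one named, error is 0.025 per outcome and at most 0.05 overall.
2. Replace the imbalance trigger with a fixed list chosen for expected prognostic value. Use only variables measured before the task (motivation, initial interest and, for the pupil outcome, the baseline pupil diameter already being recorded) or variables that the intervention cannot change (such as gender or native language, even though they are asked afterwards).
3. Self-rated writing, critical thinking and English ability are asked after the task and could be coloured by having used ChatGPT. Keep the model that adjusts for them as a sensitivity analysis, or move those items to the pre-survey. The protocol placed them late to avoid signalling effects on writing behaviour, so moving them has a price.

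The cost is a few sentences of analysis text and no new data, unless items are moved. The downside is that a chance imbalance can then be addressed only in a labelled sensitivity analysis.
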